### 2.13 Adverse events

Investigators should determine whether adverse events are related to glucocorticoids. Adverse events related to glucocorticoids mainly include infection, water-sodium retention, Cushing syndrome, poorly controlled hyperglycemia, gastrointestinal ulcer, thromboembolic disease, neuropsychiatric symptoms, osteoporosis, increased intraocular pressure, and withdrawal syndrome. If an adverse event occurs, the investigator should give appropriate medical interventions, including symptomatic treatment, dose reduction or discontinuation of glucocorticoids, and follow-up observations until the adverse event will be completely resolved. Information related to adverse events will be recorded in detail, including start and end dates, symptoms and signs, severity and frequency, management, and outcomes.

### 2.14 Protocol deviations and violations

If a procedure or behavior was not in accordance with the protocol, but did not cause any significant impact on the study endpoints, it would be defined as a minor protocol deviation, such as missing a visit window which does not affect the use of assigned treatment and assessment of efficacy per the protocol. If a procedure or behavior was not in accordance with the protocol, and led to an impact on the study endpoints or participants’ safety, it would be defined as a major protocol violation, such as inadequate informed consent, unmet eligibility criteria, unreported serious adverse events, use of prohibited medication, or missing of multiple visits.

### 2.15 Data analysis

The intention-to-treat (ITT) set comprises all participants randomized. The per-protocol (PP) set consists of participants who complete the assigned treatments of protocol and develop the primary endpoint events without major protocol violation. The safety set contains participants who receive at least one dose of local glucocorticoids and undergo at least one safety evaluation. Continuous variables are described as mean ± standard deviation and median (range) and categorical variables are described as frequencies (percentages). Whitney U test, chi-square test, and Fisher’s exact test are used, if appropriate. A two-sided P value of <0.05 is considered statistically significant. All statistical analyses are performed using IBM SPSS 26.0 software (IBM Corp, Armonk, NY, United States).

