### 2.5 Study endpoints

The primary endpoints include the recovery and improvement of ARII after treatment. The secondary endpoints include the recurrence and aggravation of ARII, and adverse events during hospitalization and follow-up periods.

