### 2.6 Sample size calculation

Sample size is calculated by using significant difference test in the proportion between two groups on the statistical software PASS 15.0.5 (NCSS, LLC. Kaysville, Utah, United States). The rates of improvement of ARII are estimated as 97.7% and 72.1% in patients treated with and without glucocorticoids according to the results of a previous study by Chen et al. (2021) An alpha value of 0.05, a power of 80%, and a dropout rate of 10% are set. Finally, 30 patients will be required for each group.

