The grade of intestinal mucosal damage on colonoscopy is evaluated in accordance with the Vienna rectal score (Wachter et al., 2000), as follows.(1) Grade 0 is defined as only localized mucosal hyperemia and edema.(2) Grade 1 is defined as diffuse non-confluent mucosal hyperemia and edema with single telangiectasia but without ulcer, stenosis, and necrosis.(3) Grade 2 is defined as diffuse and confluent mucosal hyperemia and edema with multiple non-confluent telangiectasia but without ulcer, stenosis, and necrosis.(4) Grade 3 is defined as unlimited mucosal hyperemia and edema with multiple and confluent telangiectasia, and the area of superficial ulcer is less than 1 cm^2^, but without stenosis and necrosis.(5) Grade 4 is defined as unlimited mucosal hyperemia, edema, and telangiectasia, and the area of superficial ulcer is more than 1 cm^2^, and the diameter of lumen diameter is more than 2/3 of the regular lumen diameter, but without necrosis.(6) Grade 5 is defined as unlimited mucosal hyperemia, edema, and telangiectasia with deep ulcer, fistula, or perforation, and the diameter of lumen diameter is less than 1/3 of the regular lumen diameter, and presence of necrosis.

Recovery is defined as patients’ clinical symptoms and intestinal mucosal damage on colonoscopy disappear. Improvement is defined as patients’ clinical symptoms alleviate or the Vienna rectal score decreases at least one grade.

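### As worded, the per-protocol set admits only participants who reach a favourable primary endpoint, so per-protocol improvement is 100% in both arms whatever the true effect

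*Protocol article*

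**What the plan says.** Section 2.15 defines three analysis sets. For the ITT set: "The intention-to-treat (ITT) set comprises all participants randomized". The PP set consists of participants who "complete the assigned treatments of protocol and develop the primary endpoint events without major protocol violation".

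Section 2.5 says which events these are: "The primary endpoints include the recovery and improvement of ARII after treatment". Section 2.7 defines each. The stricter of the two needs symptoms and mucosa both to clear: "Recovery is defined as patients’ clinical symptoms and intestinal mucosal damage on colonoscopy disappear". For the other, a partial change in either one is enough: "Improvement is defined as patients’ clinical symptoms alleviate or the Vienna rectal score decreases at least one grade". Both are good outcomes for the patient.

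Section 2.6 sizes the trial on improvement: "The rates of improvement of ARII are estimated as 97.7% and 72.1% in patients treated with and without glucocorticoids". It adds: "An alpha value of 0.05, a power of 80%, and a dropout rate of 10% are set". The result is 30 patients per group.

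No other section redefines the PP set or explains the verb *develop* in another sense.

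**The concern.** To develop recovery or improvement is to respond. A participant who completes treatment, attends every assessment, breaks no rule and does not improve still fails the definition. Membership of the set then depends on the outcome that the set is meant to compare.

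A PP analysis normally shows whether the ITT result holds among those treated as planned. Under this definition the comparison of improvement has only one possible result, so it can neither support nor challenge the ITT finding. If the trial truly favoured glucocorticoids, the PP table would show no difference. If it did not, the table would show the same, and a reader could mistake it for excellent response in both arms.

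**Working it through.** **Inputs.** Improvement 97.7% with and 72.1% without glucocorticoids; alpha 0.05, power 80%, dropout 10%, 30 per group (section 2.6); two-sided testing and the PP rule (section 2.15); endpoint definitions (sections 2.5 and 2.7).

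**Step 1: reproduce the plan's figure.** Two-sided z-test for two proportions with unpooled variance:

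n = (1.960 + 0.842)² × [p1(1 − p1) + p2(1 − p2)] / (p1 − p2)²

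= 7.851 × [0.977 × 0.023 + 0.721 × 0.279] / 0.256²

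= 7.851 × 0.2236 / 0.0655 = 26.8, rounded up to 27 per group.

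With 10% dropout, 27 / 0.90 = 30 per group. The stated size is reproduced, and 27 is the evaluable number per arm that the plan expects.

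**Step 2: apply the PP rule as written.** The share removed as non-responders is 1 − 0.977 = 2.3% in the glucocorticoid arm and 1 − 0.721 = 27.9% in the control arm. Of 27 evaluable, the expected numbers left are:

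- glucocorticoid: 27 × 0.977 = 26.4, about 26
- control: 27 × 0.721 = 19.5, about 19 (the unrounded 19.47 is below one half)

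These counts assume no losses beyond the planned dropout. Incomplete treatment or major violations would lower them further.

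**Step 3: compare improvement under two definitions of the set.**

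| PP set | Glucocorticoid | Control | Difference in design rates | Fisher's exact P |
|---|---|---|---|---|
| Endpoint assessed, any result | 26/27 | 19/27 | 25.6 points | 0.024 |
| As written | 26/26 | 19/19 | 0 | 1 |

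In the second row the non-responder column is empty, so the chi-square statistic cannot be computed. The zero does not depend on the design rates: any pair of true rates gives 100% versus 100%.

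**Step 4: recovery.** This depends on what the word events requires.

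- If both events are required, recovery too is 100% versus 100%.
- If either suffices, recovery is not forced. By the section 2.7 definitions, a participant whose symptoms have disappeared has also had them alleviate, so those who recover are a subset of those who improve. The PP recovery rate is then the true recovery rate divided by the improvement rate: r / 0.977 with glucocorticoids and r / 0.721 without. The control rate is inflated by 1 / 0.721 = 1.39 and the glucocorticoid rate by 1 / 0.977 = 1.02. The ratio of recovery rates is multiplied by 0.721 / 0.977 = 0.74, against glucocorticoids. With equal true recovery, the PP set would thus show glucocorticoids as worse.

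**The case against.** **A drafting slip.** The strongest reply is that the authors meant participants in whom the primary endpoint was assessed. The literal rule gives a degenerate analysis that nobody would choose, and section 2.14 describes minor deviations as those that leave the use of treatment and the assessment of efficacy intact. This reading is plausible. It does not remove the point, because the published sentence says something else, nothing in the article corrects it, and an analyst who follows it drops the non-responders.

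**Left to the analysis plan.** Detail on analysis sets often is. Here nothing is missing: the article states the definition, and the definition is wrong as written.

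**The trial's efficacy result as a whole.** A reader might infer that this result is compromised. The documents do not support that. The ITT set is everyone randomised and is untouched, and the article makes no conclusion depend on the PP set. It does not say which set is primary, but that is commonly left to an analysis plan and is no fault here.

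**Forced results for every endpoint.** A reader might also take 100% versus 100% to hold for both endpoints. It holds for improvement and for the composite of either event; for recovery it holds only if both events are required.

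**Major violations.** Section 2.14 calls a deviation major if, among other things, it "led to an impact on the study endpoints". One might infer that unblinded staff would classify violations once outcomes are known. The article does not say who classifies them or when. The same sentence also covers participants' safety, and its examples, such as unmet eligibility criteria or prohibited medication, do not turn on whether the patient improved. That inference is not supported.

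**Conclusion.** The PP definition in section 2.15 is wrong as written and should be fixed. Read literally, it selects on the primary outcome, removing 2.3% of one arm and 27.9% of the other at the design rates. The planned 25.6-point difference in improvement becomes 0 for any true effect. Recovery is either forced in the same way or compared among responders only, with its rate ratio shrunk by a factor of about 0.74 at the design rates.

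The zero difference for improvement rests only on the literal wording. The counts of about 26 and 19 rest on the section 2.6 rates, on 27 evaluable per arm and on dropout unrelated to response. The factor for recovery also treats recovery as a subset of improvement. The damage is confined to the PP analysis; randomisation, sample size, data collection and the ITT comparison are unaffected.

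**What to change.** In section 2.15, replace the words that require participants to develop the primary endpoint events with: *have an evaluable primary endpoint assessment, whatever the result*. Keep the other two conditions, completed assigned treatment and no major protocol violation.

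The cost is one phrase. No patients, visits or data are added, and the sample size does not change. If a separate analysis plan exists, its PP definition should be checked for the same wording.

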According to the current practice guidelines, glucocorticoids have been widely recommended for the management of inflammatory bowel disease due to their anti-inflammatory effects (Lamb et al., 2019). It seems that glucocorticoids should also be potentially effective for ARII, considering the importance of inflammation response in the development and progression of ARII. However, the existing evidence on the use of glucocorticoids in such patients is still inconsistent among studies (Chen et al., 2021; Kochhar et al., 1991). Besides, the current practice guideline and consensus mostly focus on the management of chronic radiation-induced intestinal injury (CRII), rather than ARII (Paquette et al., 2018; Wang and Wang, 2018). Thus, we aim to conduct a multicenter randomized controlled trial (RCT) to explore the efficacy and safety of glucocorticoids for the treatment of ARII.

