## 2 Methods

### 2.1 Study design

In this multicenter RCT, patients with grade II-III ARII will be screened. The investigators from each center will sufficiently explain the objectives and harms of this study to potentially eligible participants. Once the participants agree and sign written informed consents, they will be randomly assigned at a ratio of 1:1 to routine treatment alone and in combination with local glucocorticoids groups. The data will be collected at admission, after treatment, and during follow-up periods (Figure 1). This study follows the Declaration of Helsinki, and the ethical approval number from medical ethical committee of the General Hospital of Northern Theater Command is Y (2024) 052-1. It has been registered in the *ClinicalTrials.gov.* Website (registration number: NCT06410443).

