### 2.4 Treatment

Routine treatment includes antibiotics, probiotics, vitamins, antidiarrheal drugs, enteral nutrition, and endoscopic argon plasma coagulation according to the current practice guideline (Wang and Wang, 2018). These drugs and procedures are selected based on the patients’ disease conditions and their availability at each site.

Local glucocorticoids refer to retention enema of dexamethasone 10 mg combined with 100 mL of 0.9% sodium chloride injection once daily for a duration of 7 days. It requires the solution to be retained in the bowel for more than 1 h.

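### The safety set admits only participants given glucocorticoid enemas, so it has no control arm and cannot compare safety between the randomised groups

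*Protocol article*

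**What the plan says.** Section 2.15 of the protocol article names three analysis sets. The intention-to-treat set is everyone randomised, and the per-protocol set is a subset defined by completion and compliance. The third is defined as follows: "The safety set contains participants who receive at least one dose of local glucocorticoids and undergo at least one safety evaluation". No other safety population is named, and no sentence assigns adverse events to a different set.

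The rest of the protocol describes a two-arm comparison:

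- **Aim (section 1):** to "explore the efficacy and safety of glucocorticoids for the treatment of ARII" by means of a multicentre randomised trial.
- **Allocation (section 2.1):** participants are "randomly assigned at a ratio of 1:1 to routine treatment alone and in combination with local glucocorticoids groups".
- **Treatments (section 2.4):** "Local glucocorticoids refer to retention enema of dexamethasone 10 mg" in saline. The background care is listed separately: "Routine treatment includes antibiotics, probiotics, vitamins, antidiarrheal drugs, enteral nutrition, and endoscopic argon plasma coagulation".
- **Endpoints (section 2.5):** the secondary endpoints include "adverse events during hospitalization and follow-up periods", with no limit to one arm.
- **Collection (sections 2.9 and 2.12, Table 1):** all participants are followed, and adverse events are recorded at day 7 and at months 1, 3, 6 and 12, again without restriction by arm.
- **Attribution (section 2.13):** "Investigators should determine whether adverse events are related to glucocorticoids". Section 2.3 makes the assignment known to participants and physicians.

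**The concern.** Entry to the safety set depends on exposure to the experimental treatment. In a trial of routine care with and without that treatment, such a condition removes the comparator. Control-arm adverse events would be collected for a year and then fall outside the only population named for safety.

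This matters because many of the events listed in section 2.13 are not specific to glucocorticoids. Infection, poorly controlled hyperglycaemia, gastrointestinal ulcer and thromboembolic disease can all arise in cancer patients after pelvic radiotherapy who never receive an enema. The Discussion itself says that these patients may be in poor physical condition and that glucocorticoid adverse events have not yet been discussed in acute radiation-induced intestinal injury. The protocol gives no background rate, so the concurrent randomised controls are the only internal reference.

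Investigator attribution cannot take their place. The investigators know the allocation, and in practice they can call an event glucocorticoid-related only where a glucocorticoid was given.

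**Working it through.** **1. Planned group size.** Section 2.6 gives 97.7% versus 72.1%, alpha 0.05, power 80%, dropout 10% and 30 per group; section 2.15 makes tests two-sided. The stated size is reproduced by the unpooled two-proportion formula:

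n = (z₀.₉₇₅ + z₀.₈₀)² × [p₁(1−p₁) + p₂(1−p₂)] / (p₁−p₂)²

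= (1.960 + 0.842)² × [0.977×0.023 + 0.721×0.279] / 0.256²

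= 7.85 × 0.2236 / 0.0655 ≈ 26.8, rounded up to 27.

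27 / (1 − 0.10) = 30 per group, 60 in total. The finding does not depend on this calculation, which only supplies the group size.

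**2. Membership of the safety set as written.** Two conditions apply: at least one dose of local glucocorticoids, and at least one safety evaluation.

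| | Glucocorticoid arm | Control arm |
|---|---|---|
| Randomised (planned) | 30 | 30 |
| Meets the dose condition when treated as assigned | 30 | 0 |
| In the safety set as written | 30 | 0 |
| In a set of all treated and evaluated participants | 30 | 30 |

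The 30s assume full adherence, no crossover and one safety evaluation each. If the planned 10% dropout meant no safety evaluation, the set would hold 27 versus 0. The zero does not depend on dropout. A control participant who did receive an enema would enter as an exposed participant and would not supply an unexposed rate.

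**3. What the set can estimate (assumed counts, not in the protocol).** Suppose 6 of 30 participants in the enema arm have an infection: 6/30 = 20%, Clopper-Pearson 95% CI 7.7% to 38.6%. The excess risk is 20% minus the control rate, and this set has no control rate.

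With controls included and an assumed 3/30 = 10% among them, the risk difference is 0.20 − 0.10 = 0.10. Its standard error is √(0.20×0.80/30 + 0.10×0.90/30) = √0.00833 = 0.091. The Wald 95% CI is 0.10 ± 1.96×0.091, or about −8 to +28 percentage points. That is wide, but it estimates the right quantity.

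**4. What 30 versus 30 could detect (assumed rates, two-sided 5%).**

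| Control vs enema rate | Power, normal approximation | Power, Fisher exact |
|---|---|---|
| 10% vs 20% | 19% | 10% |
| 10% vs 30% | 49% | 37% |
| 10% vs 40% | 78% | 71% |

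The full set would therefore support estimation with intervals and detection of large differences only. The set as written supports no comparison.

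**The case against.** The strongest reply is that section 2.15 defines the sets without tying any endpoint to any of them. Adverse events could be compared in the intention-to-treat set, using the chi-square or Fisher tests that the section names. The abstract also words the secondary endpoint more narrowly than section 2.5, as adverse events of glucocorticoids. With the relatedness question in section 2.13, that suggests a descriptive account of exposed patients may have been intended, and a set of exposed patients would suit it. Finally, 30 versus 30 is too small for a strong safety test, the primary endpoints are untouched, and an unseen analysis plan might define the set differently.

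Part of this stands. The data will allow a comparison, so the limit applies to the defined set and not to the trial's records. The comparison would be imprecise. The abstract and section 2.5 also need to agree on the endpoint.

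The rest does not remove the problem. Nothing assigns adverse events to the intention-to-treat set, and a population labelled as the safety set is naturally read as the one for safety analysis. A description of glucocorticoid harms still needs a background rate when the listed events can occur without the drug and allocation is open. Low precision is a reason to report intervals, not to discard the comparator. An explicit definition that excludes controls is also a stated rule, not detail left to an analysis plan.

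**Conclusion.** The concern holds. As written, the only safety population in the protocol contains no control participant treated as assigned: 30 versus 0 where the design provides 30 versus 30. No between-arm difference in adverse events can be estimated in it, although safety is part of the trial's aim and adverse events are a secondary endpoint. The count of 30 assumes full adherence, no crossover and at least one safety evaluation each; the zero follows from the definition and the content of the control treatment. The infection counts and power figures are illustrations on assumed rates, and the conclusion does not rest on them. The definition must be corrected before any analysis, because choosing a different population after the data are seen would be a post hoc departure.

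**What to change.** In section 2.15, redefine the safety set as all randomised participants who received any assigned treatment (routine treatment alone, or routine treatment with at least one enema) and had at least one safety evaluation, analysed by treatment received.

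State that all adverse events, whatever their judged cause, will be tabulated by arm with risk differences and 95% confidence intervals. Keep the investigator's relatedness judgement as a descriptive column. Word the adverse-event endpoint in the abstract to match section 2.5.

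The cost is one sentence for the definition, one for the tabulation and a wording change in the abstract. Control-arm adverse events are already scheduled in Table 1, so no visit, procedure, treatment or sample size changes.

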### 2.8 Data collection

The following data will be collected: (1) demographic data (i.e., gender and age); (2) history of malignancy; (3) interval between radiotherapy and occurrence of ARII; (4) history and type of medications for ARII before admission; (5) height, weight, and vital signs (i.e., body temperature, heart rate, blood pressure, and respiratory rate); (6) clinical symptoms (i.e., abdominal pain, distension, diarrhea, frequency of defecation, tenesmus, hematochezia, mucous stool, nausea, vomiting, acid reflux, and heartburn); (7) laboratory data (i.e., red blood cells, hemoglobin, white blood cells, neutrophils, lymphocytes, procalcitonin, c-reactive protein, IL-6, IL-2, TNF-α, IFN-γ, potassium, sodium, calcium, iron, and stool routine test); (8) grade of intestinal mucosal damage on colonoscopy; (9) histology of colorectal mucosa; and (10) intestinal obstruction, fistula, perforation, and/or stricture.

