### 2.12 Study schedule

The study treatment and assessment plan are summarized in Table 1.(1) Eligible participants will be enrolled after signing their informed consents.(2) Demographic data, medical history, clinical symptoms, physical examinations, laboratory tests, abdominal computed tomography (CT) images, and description under colonoscopy will be collected before treatment.(3) Repeated abdominal CT scans will be performed on the 6th month after treatment.(4) Repeated colonoscopy will be performed on the 3rd month and 12th month after treatment.(5) Adverse events and survival status will be collected on the 7th day, 1st month, 3rd month, 6th month, and 12th month after treatment.

**TABLE 1 T1:** Study schedule.

Procedure	Screening	Treatment period 7th day	Follow-up period			
			1st month	3rd month	6th month	12th month
Informed consent	√					
Eligibility criteria	√					
Demographic data	√					
Medical history	√					
Clinical symptoms	√	√	√	√	√	√
Physical examinations	√	√	√	√	√	√
Laboratory tests	√	√	√	√	√	√
Abdominal computed tomography	√				√	
Colonoscopy	√			√		√
Adverse events		√	√	√	√	√

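### Recovery is compared with crude two-group tests although the baseline Vienna grade it plausibly depends on is already collected; adjusting for it and for the stratification factor would be a cheap gain in precision

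*Protocol article*

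**What the plan says.** Section 2.15 (Data analysis) lists the tests as "Whitney U test, chi-square test" and Fisher's exact test, with the rule "A two-sided P value of <0.05 is considered statistically significant". No covariate or stratified analysis is named.

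Section 2.3 stratifies randomisation by the grade of ARII at admission and nothing else. Section 2.7 defines that grade by symptoms, treatment need and complications. The Vienna rectal score, in the same section, is a separate endoscopic scale.

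Under section 2.7, recovery means that both symptoms and colonoscopic mucosal damage are gone. Improvement means that symptoms ease or that "the Vienna rectal score decreases at least one grade".

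The baseline value is available: section 2.8 lists the "grade of intestinal mucosal damage on colonoscopy" as a data item, section 2.12 states that "description under colonoscopy will be collected before treatment", and Table 1 ticks colonoscopy at screening.

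**The concern.** A participant who enters with mild, localised mucosal change has less to clear than one who enters with ulceration, so the chance of recovery plausibly depends on the starting Vienna grade. Randomisation does not balance that grade directly, and the named tests do not use it. They also leave out ARII grade, the factor on which randomisation was stratified.

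Two things are at stake for recovery. One is precision: between-patient variation that a recorded baseline value could explain stays in the comparison. The other is how a single result is read. With about 30 per arm, a visible chance difference in baseline mucosal severity is quite possible, and in an open-label trial without a pre-specified adjustment it would invite argument after the fact.

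**Working it through.** **1. The protocol's own figure.** Section 2.6 gives the inputs: "The rates of improvement of ARII are estimated as 97.7% and 72.1% in patients treated with and without glucocorticoids". Alpha is 0.05, power is 80% and allowance is made for 10% dropout; the stated size is 30 per arm. A two-sided unpooled Z test for two proportions gives

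n = (1.960 + 0.842)² × (0.977×0.023 + 0.721×0.279) / (0.977 − 0.721)² = 7.85 × 0.2236 / 0.0655 = 26.8, so 27 per arm.

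27 / 0.90 = 30, which reproduces the stated size. It concerns improvement only; the article gives no rates for recovery.

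**2. Chance imbalance.** For a binary high/low Vienna factor with 30 per arm and no stratification on it (hypergeometric), the arms differ by at least 20 percentage points with probability 16% at 30% prevalence and 20% at 50% prevalence.

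On the ordinal scale, assume grades 0–4 at 15/25/30/20/10% (SD about 1.2). The SE of the difference in means with 27 per arm is 1.2 × √(2/27) = 0.33. Before that rounding, 1.195 × 0.272 = 0.325 and 1.96 × 0.325 = 0.64, so about 5% of trials differ by 0.64 grade or more. At a slope of 0.8 log-odds per grade, such a difference is worth an odds ratio of about exp(0.8 × 0.64) = 1.7 in that one trial. These probabilities ignore any indirect balance from stratifying on ARII grade.

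**3. Recovery: crude against adjusted.** Assumptions, none of them in the article: recovery 30% vs 60%, 27 per arm, the Vienna distribution above, and log-odds of recovery falling by 0.5, 0.8 or 1.2 per grade. The main run had 3,000 simulated trials per scenario, so the Monte Carlo SE near 58% is √(0.58×0.42/3000) = 0.9 point.

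| Slope per grade | Crude chi-square | Logistic, arm + Vienna grade |
|---|---|---|
| 0.5 | 58.3% | 65.8% |
| 0.8 | 58.8% | 71.2% |
| 1.2 | 58.1% | 76.0% |

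Repeat runs gave 58–59% crude and 64–66%, 69–71% and 76% adjusted. With 30% in both arms, chi-square rejected in 4.4–5.1% of trials and the logistic likelihood-ratio test in 5.2–6.0%. At zero slope the adjusted test still showed 59.7% vs 56.3%, a difference of 3.4 points that cannot come from prognosis. Taking off about 3 points leaves a gain of roughly 3–5 points at slope 0.5 (64–66 − 58 − 3) and 15 at slope 1.2 (76 − 58 − 3).

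**4. A check nearer the article's figures.** The Discussion reports mucosal repair of 93.02% vs 65.12% in the earlier trial. That is a different endpoint, but the closest available. At those rates and 27 per arm, crude chi-square has about 77% power and adjusted logistic regression about 79%, 82% and 86% at the three slopes.

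**5. Improvement.** At 97.7% vs 72.1% with 27 per arm, about 27 × (0.023 + 0.279) = 8.2 failures are expected. A Cochran-Mantel-Haenszel (CMH) test stratified by Vienna 0–1 vs 2 or more gave, at slopes 0/0.5/0.8/1.2, 82.3/83.3/83.7/85.7%, against 85.3/84.9/85.3/85.5% for chi-square. The change runs from −3.0 to +0.2 points, so there is no gain.

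**The case against.** The strongest reply is that nothing here is wrong. Chi-square and Fisher are valid for a randomised binary comparison. Chance imbalance is already covered by the error rate and does not bias the comparison on average. A reader might infer that leaving out the Vienna grade inflates type I error or makes the recovery result untrustworthy; the runs at about 5% do not support that. The odds ratio of 1.7 describes only the most imbalanced trials, under an assumed slope.

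A reader might also infer that the whole primary analysis loses power, because the mucosal endpoints look like changes in Vienna grade. Recovery is an end state, not a change. The Vienna fall is one of two alternative routes to improvement, and symptom relief alone suffices, so a participant at Vienna grade 0 can still improve. At the only rates for which the trial is sized, stratifying on the grade brings no benefit.

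The inputs for recovery are chosen, not documented. A slope of 1.2 is an odds ratio of exp(4.8), about 120, between grades 0 and 4; 0.8 gives exp(3.2), about 25. Excluding severe gastrointestinal ulcers may narrow the Vienna range, and stratifying on ARII grade may balance it in part; the article gives no correlation. An analysis plan that is not shown may already adjust.

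All of this limits the size of the point. What stands is that section 2.15 does name its tests, that they are unadjusted, and that the relevant baseline value is already in the data set.

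**Conclusion.** The point holds for recovery as an improvement in efficiency and robustness. The crude tests keep about their nominal level. If the baseline Vienna grade is prognostic, adjustment raises power from about 58% to about 64–76% under the assumed 30% vs 60%, 27 per arm and slopes of 0.5–1.2, with about 3 points of that not attributable to the covariate. If the grade is weakly prognostic, or recovery rates are far from mid-range, the gain is smaller and may be negligible. The point does not extend to improvement and does not affect the sample size calculation. That the named tests also omit ARII grade, the stratification factor, follows from the text and needs no assumption.

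**What to change.** In section 2.15, specify that recovery is analysed by logistic regression on treatment arm, ARII grade (the stratification factor) and baseline Vienna grade as an ordinal covariate, reported as a standardised risk difference with 95% CI. Keep chi-square/Fisher as a sensitivity analysis. State in advance a fallback, such as penalised estimation, in case recovery is too rare or too common for the model to fit. Do not add a Vienna-stratified test for improvement.

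The cost is wording: no extra patients, visits or data, and the named SPSS software can fit the model. There is one small downside. The likelihood-ratio test ran at about 5–6% type I error at this sample size. That figure is for a model with arm and Vienna grade only, so the version with ARII grade added should be checked by a short simulation before the plan is fixed. The change should be made before outcome data are compared by arm.
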